## Abstract

**Background:**

Multi-month dispensing (MMD) is the mainstay mechanism for clinically stable people living with HIV in Cambodia to refill antiretroviral therapy (ART) every 3-6 months. However, less frequent ART dispensing through the community-based ART delivery (CAD) model could further reduce the clients’ and health facilities’ burden. While community-based services have been recognized as an integral component of HIV response in Cambodia, their role and effectiveness in ART delivery have yet to be systematically assessed. This study aims to evaluate the CAD model’s effectiveness on the continuum of care and treatment outcomes for stable people living with HIV in Cambodia.

**Methods:**

We will conduct this quasi-experimental study in 20 ART clinics across the capital city and nine provinces between May 2021 and April 2023. Study sites were purposively selected based on the availability of implementing partners, the number of people living with HIV each clinic serves, and the accessibility of the clinics. In the intervention arm, approximately 2000 stable people living with HIV will receive ART and services from the CAD model. Another 2000 stable people living with HIV in the control arm will receive MMD—a standard care model for stable people living with HIV. The primary outcomes will be retention in care, viral load suppression, and adherence to ART. The secondary endpoints will include health providers’ work burden, the model’s cost-effectiveness, quality of life, mental health, social support, stigma, and discrimination. We will compare the outcome indicators within each arm at baseline, midline, and endline using descriptive and inferential statistics. We will evaluate the differences between the intervention and control arms using the difference-in-differences method. We will perform economic evaluations to determine if the intervention is cost-effective.

**Discussion:**

This study will build the evidence base for future implementation and scale-up of CAD model in Cambodia and other similar settings. Furthermore, it will strengthen engagements with community stakeholders and further improve community mobilization, a vital pillar of the Cambodian HIV response.

**Trial registration:**

ClinicalTrials.gov, NCT04766710. Registered 23 February 2021, Version 1.

**Supplementary Information:**

The online version contains supplementary material available at 10.1186/s12879-021-06414-y.

## Background

Cambodia has substantially reduced the prevalence of human immunodeficiency virus (HIV) in the general adult population aged 15–49 years from 1.7% in 1998 to 0.5% in 2019 [1, 2]. Cambodia is also one of the three countries in the Asia-Pacific region to have achieved the UNAIDS 90–90-90 targets. More than 90% of people living with HIV receiving antiretroviral therapy (ART), and 80% had viral suppression [3]. Despite the successes, there are persistent concerns regarding attrition from HIV testing and linkages to care and the retention in care, especially among members of the hidden populations in Cambodia [4]. A recent systematic review and meta-analysis of studies in low- and middle-income countries reported that groups with vulnerable socioeconomic and clinical status and social support were at increased risk of loss to follow-up from ART programs [5]. From the health systems perspective, care providence at a higher level was associated with a higher risk of attrition from the treatment cascade [5]. Therefore, through decentralization of care and community involvement, differentiated ART delivery models that are contextualized could improve care retention and sustain treatment outcomes [6, 7].

In Cambodia, ART is primarily administered at 68 public ART clinics across 25 provinces [8]. Clinics operated by several non-governmental organizations (NGOs) also complement the ART services. However, regular clinic runs and ARV refills posed a heavy resource burden on people living with HIV to remain optimally engaged in care [9]. Besides, it also contributed significant workload on the health facilities and service providers to meet the demands of both stable people living with HIV and unstable people living with HIV, who required more frequent follow-ups [10]. Hence, a differentiated care model would enable health providers to invest more time on unstable and complicated cases, thus improving overall service quality [10]. An appointment-spacing and multi-month dispensing (MMD) model has been introduced to all ART clinics to increase service efficiency and decrease congestion by reducing clinical visits and refill appointments for stable people living with HIV [11]. However, concerns regarding sub-optimal storage of antiretrovirals (ARVs), poor adherence, and missed appointments have emerged [12].

Community-based service delivery plays an integral part in the HIV response in many countries, including Cambodia [1, 13–17]. A study conducted among people living with HIV in Cambodia expressed the need for community-based interventions to reduce stigma and discrimination among the general public and support people living with HIV to address these stressful situations [18]. In 2016, the World Health Organization (WHO) recommended that stable people living with HIV can safely reduce the frequency of clinic visits by potentially receiving ART in community settings [13]. Compared to hospital-based settings, decentralizing HIV treatment delivery and task shifting to include community health workers to dispense ART was reported to improve retention across the HIV care cascade [19]. Community-based ART delivery (CAD) models implemented outside Cambodia have reduced burdens for people living with HIV and the health systems, increased retention in care, and lowered overall service provider costs [20–24].

The two promising differentiated care models (i.e., MMD and CAD) have yet to be fully implemented and evaluated in Cambodia. Hence, little is understood on the operationality and effectiveness of the models in improving the care of people living with HIV. The primary aim of this study is to implement and evaluate the effectiveness of CAD compared to MMD on the care continuum and treatment outcomes for stable people living with HIV. We will also determine the acceptability, feasibility, barriers, and facilitators to implementing the CAD model in Cambodia. We hypothesize that a significantly higher proportion of participants in the intervention arm will report viral load suppression, retention in care, good ART adherence, improved quality of life and mental health, a better sense of social support, and lower stigma and discrimination. We also hypothesize that the CAD model will be more cost-effective compared to MMD (control arm). A significantly higher proportion of health care providers at the ART clinics in the intervention arm is also postulated to report reduced workload and lower burnout scores due to the implementation of CAD.

## Methods

### Design

We will conduct a quasi-experimental study [25, 26] consisting of two arms—intervention and control for 24 months. Approximately 2000 stable people living with HIV in the intervention arm will receive services from the CAD model. Another 2000 people living with HIV in the control arm will receive MMD—a default care model for stable people living with HIV to refill ART every 3-6 months with a routine 6-monthly clinical review. We will adopt an effectiveness-implementation hybrid design type II [27], where a mixed-methods approach will run in parallel to evaluate the effectiveness (quantitative) and implementation strategy (qualitative).

### Settings

This study will include 10 ART clinics in Phnom Penh capital city and four provinces (Kampong Thom, Kampot, Koh Kong, and Takeo) for the intervention arm (Table 1). We will include 10 other ART clinics in Phnom Penh and five provinces (Kampong Cham, Pailin, Preah Sihanouk, Siem Reap, and Prey Veng) for the MMD control arm (Table 1). These sites have been purposively selected based on (i) the availability of implementing partners (Cambodian People Living with HIV Network, ARV User Association, and Partner in Compassion), (ii) the number of eligible people living with HIV for enrollment in the intervention and control arms, and (iv) advice from the national HIV program on the accessibility of the clinics.

**Table 1 Tab1:** Study sites for the quasi-experimental study to evaluate the CAD model

Intervention sites			Control sites		
Province	ART clinic	Setting	Province	ART clinic	Setting
Kampot	Kampot Hospital	Urban	Kampong Cham	Kampong Cham Hospital	Urban
Kampot	Kampong Trach Hospital	Rural	Kampong Cham	Cheung Prey Hospital	Rural
Koh Kong	Smach Meanchey Hospital	Urban	Pailin	Pailin Hospital	Urban
Koh Kong	Sre Ambil Hospital	Rural	Preah Sihanouk	Preach Sihanouk Hospital	Urban
Phnom Penh	Mean Chey Hospital	Urban	Phnom Penh	Chhouk Sar I Clinic	Urban
Phnom Penh	Pochintong Hospital	Urban	Phnom Penh	Sam Dach Ov Hospital	Urban
Kampong Thom	Kampong Thom Hospital	Urban	Siem Reap	Siem Reap Hospital	Urban
Kampong Thom	Baray Santok Hospital	Rural	Siem Reap	Soth Nikum Hospital	Rural
Takeo	Takeo Hospital	Urban	Prey Veng	Prey Veng Hospital	Urban
Takeo	Kirivong Hospital	Rural	Prey Veng	Neak Loeung Hospital	Rural

*ART* antiretroviral therapy, *CAD* community ART delivery

### Participants

We define stable people living with HIV as individuals who (i) are ≥15 years, (ii) have received first-line ART for at least 1 year, (iii) did not report ART-related adverse reactions or drug interactions requiring regular monitoring; (iv) do not have tuberculosis (presumptive/confirmed), other opportunistic infections, and are not taking any prophylactic treatment; (v) are not pregnant or breastfeeding (for women); (vi) have a good understanding of lifelong treatment and adherence to medication; and (vii) have achieved treatment success—two consecutive undetectable viral load and/or CD4 counts above 200 cells/mm^3^ [11, 19, 28]. We will conduct in-depth interviews and focus group discussions with people living with HIV, representatives of the communities, government officials at different levels (community, health centers, operational districts, provincial health departments, and national programs), local and international NGOs, donors and other developmental partners in Cambodia to explore the acceptability, barriers, and facilitators to implementing the CAD model.

### Sample size calculation

A target sample size of approximately 2000 stable people living with HIV is required to provide at least 80% power to detect a 10% relative difference retention in care or maintenance of viral suppression. The sample size calculation was based on 10% attrition and conservative estimates of retention in care or viral-suppression maintenance: 50 and 55% maintenance of viral suppression in the MMD (control arm) and CAD (intervention arm), respectively. Findings from a recent randomized controlled trial in high- and medium-HIV-prevalence settings of people living with HIV with detectable viral load showed that CAD increased viral suppression compared to the control group (74% vs. 63%, RR 1.18, 95% CI 1.07–1.29). Under similar scenarios, our proposed study’s power with 2000 participants in each arm will be at least 90%.

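### The 80% power for 50% vs 55% treats participants as independent, although the arms are 10 whole clinics against 10 others

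*Protocol article*

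**What the plan says.** The Design section of the protocol article sets two arms of equal size: "Approximately 2000 stable people living with HIV in the intervention arm will receive services from the CAD model. Another 2000 people living with HIV" serve as controls. The Settings section shows that an arm is a set of clinics: "This study will include 10 ART clinics in Phnom Penh capital city and four provinces" for the intervention. Ten other clinics form the control arm, and all 20 were chosen purposively. In Table 1 only Phnom Penh appears in both arms.

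The Sample size calculation section states that "approximately 2000 stable people living with HIV is required to provide at least 80% power to detect a 10% relative difference", for either retention or suppression. It names its inputs: "The sample size calculation was based on 10% attrition", together with "50 and 55% maintenance of viral suppression in the MMD (control arm) and CAD (intervention arm), respectively". It then cites an earlier randomised trial in which "CAD increased viral suppression compared to the control group (74% vs. 63" percent), and says that under similar conditions the study's "power with 2000 participants in each arm will be at least 90" percent. The section contains no number of clinics, ICC or design effect.

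**The concern.** When whole clinics make up the arms, participants at one clinic share staff, population and local practice, so their outcomes are correlated. The variance of the difference between arms then depends mainly on how much clinics differ and on there being only 20 of them. The article itself gives reasons to expect such differences. The sites are urban and rural hospitals in different provinces. In the control arm the refill interval is left to each clinic. In the intervention arm care is given in monthly group sessions by workers attached to a clinic.

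A calculation that counts 4,000 independent people overstates the information available. Retention and viral suppression are primary outcomes meant to inform scale-up. A null result read against a claimed 80% power would be taken as evidence against a 5-point benefit that the study may have had little chance of detecting.

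**Working it through.** **Inputs from the article.** 50% vs 55%; 63% vs 74% for the second statement; 10% attrition; 2,000 per arm; 10 clinics per arm.

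**Assumptions.** Two-sided 5% significance (not stated in the article). Equal clinic sizes, so 2,000 / 10 = 200 enrolled and 200 × 0.9 = 180 evaluable per clinic. An ICC range of 0 to 0.05, as the article gives none.

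**Step 1: reproduce the plan's figure, with participants independent.**

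n per arm = [1.96 √(2 × 0.525 × 0.475) + 0.8416 √(0.50 × 0.50 + 0.55 × 0.45)]² / 0.05² = 1,565.

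With attrition: 1,565 / 0.9 = 1,739 enrolled per arm. Power with 1,800 evaluable per arm is 85%. So 2,000 per arm supports at least 80% under independence. Reading 2,000 as the total for both arms does not: 900 evaluable per arm gives 57%.

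**Step 2: the room left for clustering.** 2,000 / 1,739 = 1.15. Setting 1 + 179 × ICC = 1.15 gives ICC = 0.15 / 179 ≈ 0.0008.

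**Step 3: power with clinics as clusters.**

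- Design effect: DE = 1 + (180 − 1) × ICC.
- Standard error: SE = √{[p₁(1 − p₁) + p₂(1 − p₂)] / 1,800 × DE}.
- Degrees of freedom: 2 × (10 − 1) = 18. Power comes from a non-central t with non-centrality |p₂ − p₁| / SE; the normal approximation is shown beside it.

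Example at ICC 0.01: DE = 1 + 1.79 = 2.79; effective n = 1,800 / 2.79 = 645 per arm; SE = √(0.4975 / 1,800 × 2.79) = 0.0278; non-centrality = 0.05 / 0.0278 = 1.80; power 40% (t) or 44% (normal).

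| ICC | DE | Effective n per arm | 50% vs 55%: t, 18 df | 50% vs 55%: normal | 63% vs 74%: t, 18 df | Difference from 50% detectable with 80% power (t) |
|---|---|---|---|---|---|---|
| 0 | 1.00 | 1,800 | 81% | 85% | >99% | 4.9 points |
| 0.005 | 1.90 | 950 | 54% | 59% | 99.8% | 6.8 points |
| 0.01 | 2.79 | 645 | 40% | 44% | 98% | 8.2 points |
| 0.02 | 4.58 | 393 | 27% | 29% | 89% | 10.5 points |
| 0.05 | 9.95 | 181 | 15% | 16% | 57% | 15.2 points |

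**Step 4: where each claim breaks.**

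- 80% for 50% vs 55%: lost above an ICC of about 0.0002 (t) or 0.0009 (normal).
- 90% for 63% vs 74%: lost above an ICC of about 0.019 (t) or 0.022 (normal).

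**Scale.** At a 50% rate the between-clinic standard deviation is √(ICC × 0.25). ICC 0.0009 means 1.5 percentage points. ICC 0.01 means 5 points, the size of the effect sought.

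**The case against.** - **The loss rests on an assumed ICC.** This is true, and the individual power figures are scenarios. That 2,000 leaves room for a design effect of only 1.15 is not a scenario: it follows from the article's rates, attrition and target size once a two-sided 5% test is taken.
- **The 90% statement is not shown to be false.** This stands. It is tied to 63% vs 74% and holds up to an ICC of about 0.02. It ignores clustering in the same way, but should be called undemonstrated.
- **50% is a deliberately conservative rate.** The Background reports 80% viral suppression, and participants enter already stable. With 80% taken as the control rate and the same 10% relative gain (80% vs 88%), the t-based power is 99.5%, 96%, 83% and 51% at ICC 0.005, 0.01, 0.02 and 0.05. The study may thus be well powered for a larger absolute difference at a higher rate. That does not rescue the published statement, which attaches 80% to 50% vs 55%.
- **The analysis may recover precision.** Difference-in-differences and covariate adjustment can remove stable clinic differences. The gain cannot be computed from the article. It is probably small for retention and suppression, because everyone is in care and treatment-stable at entry. A clinic term in a mixed model would correct the standard error but would not restore the power.
- **A fuller document may name an ICC.** It could, but it could not make the printed sample size and clinic numbers give 80% for 5 points unless the ICC were close to zero. Unequal clinic sizes would tend to lower power further.

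**Conclusion.** The concern holds. The stated 80% power for 50% vs 55% is the power of a study with independent participants, and this design assigns whole clinics. With 10 clinics per arm and 180 evaluable in each, a two-sided 5% test on 18 degrees of freedom has 54% power at ICC 0.005 and 15% at 0.05. The claim needs an ICC below about 0.001 on either reference distribution. These figures assume equal clinic sizes and a comparison at one time point. The 90% claim for 63% vs 74% shares the omission but is met for ICCs up to about 0.019.

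**What to change.** Keep the 20 clinics and 2,000 participants per arm, and replace the power statement. The new paragraph should:

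- give the number of clinics and the expected evaluable number per clinic;
- multiply the variance by 1 + (m − 1) × ICC and use a t reference with 18 degrees of freedom;
- take the ICC from clinic-level retention and suppression in the national HIV programme's database;
- report power for 50% vs 55% and for 63% vs 74%, or the minimum detectable difference, over an ICC range such as 0.005 to 0.05;
- state the significance level and that 2,000 is per arm.

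The cost is one rewritten paragraph and a request for clinic-level data. No patients or clinics are added. The stated power becomes less favourable, and the paragraph should say plainly which differences the study can and cannot be expected to detect.

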### Recruitment

We will develop a list of participating ART clinics in consultation with the Database Management Unit of the National Center for HIV/AIDS, Dermatology, and STD (NCHADS) and the other implementing partners. Potential people living with HIV will be jointly identified by the study team and clinicians on-site based on the eligibility criteria. We will seek consent from eligible people living with HIV and recruit them into the study. To measure the impact of CAD on the work burden of healthcare providers, we will recruit all staff working for the HIV program at the intervention and control sites—nurses, counselors, laboratory technicians, pharmacists, and clinicians. For the qualitative study, we will purposively recruit interviewees at the national level and intervention sites for diverse views. Schedule of enrolment, intervention, and assessments is shown SPIRIT Figure (Supplementary Material 1).

### Intervention: CAD model

People living with HIV in the intervention arm will receive antiretrovirals (ARVs) from the community action workers (CAWs) through the CAD model. We will recruit people living with HIV in the community to be CAWs. Training will be provided by the ART clinics and implementing partners on ART dispensing, drug storage, vital signs assessment and documentation, HIV education and counseling, ART adherence and measurement, referral systems, and aspects such as mental health, stigma and discrimination, and sexual and reproductive health. CAWs will obtain pre-packaged ARVs once a month from the attached ART clinic and dispense them to people living with HIV in the community. CAWs will conduct group follow-up sessions monthly to record vital signs, monitor adherence, and provide health education and counseling. Those who are unwell will be referred to the ART clinic. CAWs will also submit the relevant records to the ART clinic at their next visit. Trained clinicians will conduct ARV regimen and HIV clinical management in the ART clinics. People living with HIV in the intervention arm will visit the ART clinics for routine clinical review every 6 months and on an ad-hoc basis if medical attention is required. The study flowchart is presented in Fig. 1.

**Fig. 1 Fig1:**
[figure not shown]
Study flowchart in the intervention (community ART delivery) and control arms (multi-month dispensing model). Notes: The department/profiles in red represent the workforce required at the ART clinics to facilitate and implement MMD and CAD. Boxes in green represent activities that will occur in the ART clinics. Boxes in yellow represent activities that will occur in the community

### Control: MMD model

People living with HIV in the control arm will visit ART clinics and collect their ARVs from the facility-based service providers through the MMD model, the standard care for stable people living with HIV. People living with HIV will refill their prescriptions at the ART clinic every 3-6 months. The exact frequency might differ between individuals, decided at the discretion of individual ART clinics. People living with HIV will visit the ART clinic on an ad-hoc basis for consultation if needed. They will otherwise undergo routine clinical review every 6 months. Clinical management of people living with HIV in the intervention and control group will be done by trained personnel at the ART clinic following the national guideline [28].

### Outcome measures

We present the conceptual framework reflecting the outcome measures and their effects on the continuum of care in Fig. 2. Our primary outcomes will include (i) viral load suppression, (ii) retention in care, and (iii) adherence to ART. Viral load suppression is defined as at least 90% of the study participants in the intervention arm will have a viral load of < 1000 RNA copies/mL at the end of the intervention period. We define care retention as the proportion of people living with HIV who will remain in HIV care and treatment 12 and 24 months after study commencement. Treatment adherence will be self-reported, and we will present the proportion of people living with HIV with good adherence to ART based on standard cut-offs.

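### The primary outcome of viral load suppression is defined as a 90% target in the intervention arm alone, which contradicts the planned comparison of CAD with MMD

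*Protocol article*

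**What the plan says.** The protocol article names three primary outcomes under Outcome measures. The first opens: "Viral load suppression is defined as at least 90% of the study participants in the intervention arm". The rest of that sentence sets the threshold, under 1000 copies/mL, and places it at the close of the intervention. The sentence names one arm, sets a pass mark for it and gives one time point. The control arm does not appear.

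The retention definition that follows takes another form: "We define care retention as the proportion of people living with HIV who will remain in HIV care and treatment 12 and 24 months", counted from the start of the study. It is a proportion, tied to neither arm and with no target. Adherence is also a proportion of participants.

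Elsewhere the study is comparative:

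- **Background:** the hypothesis is that "a significantly higher proportion of participants in the intervention arm will report viral load suppression".
- **Sample size calculation:** the study is sized on "50 and 55% maintenance of viral suppression in the MMD (control arm") and CAD respectively, a between-arm contrast.
- **Data analyses:** effectiveness is evaluated by difference-in-differences, within and between arms, at baseline, midline and endline.

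No other section restates viral suppression as a variable measured in the same way in both arms.

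**The concern.** An outcome definition should give each participant a value that can be summarised by arm and compared. This one gives a single yes/no answer for the intervention arm at one time point. Taken at its word, it supplies no control value and no baseline or midline value, so none of the contrasts in Data analyses can be formed from it.

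Two incompatible criteria are left for a primary outcome: reaching 90% in CAD, or doing better than MMD. They can disagree. Allocation is not randomised, which the Discussion acknowledges, so the choice of criterion should be closed before results are seen. Otherwise a report that the 90% mark was reached would be faithful to the published definition and yet say nothing about CAD against MMD.

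The entry criteria make disagreement plausible. Participants must already have treatment success, shown by "two consecutive undetectable viral load and/or CD4 counts above 200" cells/mm³, so suppression may be high in both arms.

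**Working it through.** **1. The plan's own figures.** Inputs from Sample size calculation: 50% (MMD) versus 55% (CAD), 10% attrition, 2,000 per arm. Two-sided alpha of 0.05 is an assumption, since the article states none. Clustering by clinic is ignored throughout this step.

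n per arm = [z(0.975)·√(2·p̄·(1−p̄)) + z(0.80)·√(p1(1−p1) + p2(1−p2))]² / (p2−p1)², with p̄ = 0.525

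= [1.96 × 0.7062 + 0.8416 × 0.7053]² / 0.05² = 1,565

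After attrition: 1,565 / 0.9 = 1,739 per arm. With 2,000 enrolled, 2,000 × 0.9 = 1,800 are evaluable per arm, and power is Φ[(0.05·√1800 − 1.384) / 0.7053] = Φ(1.045) = 85.2%. The stated minimum of 80% holds. For the second scenario, 63% versus 74%, power exceeds 99.9%, so the stated minimum of 90% also holds. Both calculations treat suppression as a participant-level proportion compared between two arms, which the definition in Outcome measures is not.

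**2. How the 90% criterion behaves if used as written.** Take 1,800 participants with an observed viral load in CAD, so at least 0.9 × 1,800 = 1,620 must be suppressed. The exact binomial probability of meeting the mark depends only on the true CAD rate:

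| True CAD rate (assumed) | Probability that the mark is met |
|---|---|
| 55% (the planning rate) | about 0 |
| 88% | 0.4% |
| 89% | 9.2% |
| 90% | 52.0% |
| 91% | 93.4% |
| 92% | 99.9% |

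Check at 92% by normal approximation: SE = √(0.92 × 0.08 / 1800) = 0.0064; (0.92 − 0.90) / 0.0064 = 3.13; Φ(3.13) = 99.9%.

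Sensitivity to clustering, with an assumed ICC of 0.01 and 10 intervention clinics of 180 each: design effect = 1 + 179 × 0.01 = 2.79; SE = 0.0064 × √2.79 = 0.0107; Φ(1.87) = about 97%.

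**3. The control arm.** No control rate enters step 2. Suppose, for illustration, that MMD is at 95% and CAD at 92%. The mark is still met with probability 99.9%. A two-arm comparison with 1,800 per arm would have power Φ[(0.03·√1800 − 1.96 × 0.3486) / 0.3480] = Φ(1.69) = 95.5%, ignoring clustering, to show that CAD is worse.

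**4. The denominator.** The definition refers to the study participants in the arm, about 2,000. If the 10% lost are counted as not suppressed, a 92% rate among the 1,800 observed gives 0.92 × 1,800 = 1,656, and 1,656 / 2,000 = 82.8%, below the mark. With 10% lost, the most that can be reached is 1,800 / 2,000 = 90%, which requires every retained participant to be suppressed. Whether the mark is met therefore turns on a denominator that the article does not fix.

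**The case against.** The strongest reply is that the intent is plain. The sentence contains a usable participant-level threshold and time point, below 1000 copies/mL at the end of the intervention, which applies equally well in the control arm. The Abstract, Background, Sample size calculation and Data analyses all describe a comparison of CAD with MMD. Variables and measurements takes viral load from clinic records with no restriction by arm. Nowhere is the 90% figure made the test of effectiveness; Data analyses gives that role to difference-in-differences. All of this stands. A reader might infer that the trial has no control comparison for viral load, or cannot answer its question. The documents do not support that: the comparison is planned, and the definition is inconsistent with it.

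A second reply is that the 50% and 55% rates are labelled conservative, so a target above them is not in itself a contradiction. That also stands. The conflict with the sample size section is one of kind: that section powers a between-arm difference, while the definition sets a one-arm mark.

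A third reply is that the size of the problem rests on assumed rates. It does. No section gives 24-month suppression in stable patients for either arm, and the table shows how steeply the result changes around 90%.

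None of these replies removes the defect. The article does state a definition for this primary outcome, and what it states is a one-arm target. This is not a detail left to an analysis plan.

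**Conclusion.** The definition of viral load suppression is wrong as written and contradicts the hypothesis, the sample size basis and the analysis in the same article. This conclusion needs no numerical assumption.

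Its possible consequence is conditional. The literal criterion could be met while CAD does worse than MMD, provided that true CAD suppression is somewhat above 90%, control is higher still, and the denominator is participants with an observed viral load. At an assumed 92% the probability of meeting it is about 99.9% ignoring clustering, or about 97% at an assumed ICC of 0.01. A reader might go further and infer that the mark would be met whatever CAD does. The documents do not support that: with the 10% lost counted as not suppressed, the same 92% becomes 82.8% and misses, and at an observed-case rate of 88% the mark is met with probability 0.4%.

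This is a contradiction that rewording cures, not a flaw in the design. It should be settled before outcome data are examined.

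**What to change.** Replace the sentence in Outcome measures with a participant-level definition that applies to both arms: the proportion of participants in each arm with a viral load below 1000 copies/mL at the end of the intervention, and at the other time points used in the difference-in-differences analysis. State that the effect measure is the between-arm contrast already described in Data analyses. If the 90% figure is wanted, keep it as a separate descriptive programme benchmark and say that it is not a criterion of effectiveness.

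The cost is a short clarification of the protocol, with the registered outcome aligned if it carries the same wording. The sample size was already calculated for a comparison of this kind, and viral load is already to be taken from clinic records, so neither needs to change. The denominator and the handling of missing viral loads may be set in the statistical analysis plan; step 4 of the working shows why they should be fixed in advance.
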